# Multifactorial intervention for hip and pelvic fracture patients with mild to moderate cognitive impairment: study protocol of a dual-centre randomised controlled trial (OF-CARE)

**DOI:** 10.1186/s12877-019-1133-z

**Published:** 2019-04-30

**Keywords:** RCT, Multifactorial, Home-based, Exercise program, Care counselling, Lay instructor, Elderly, Hip or pelvic fracture, Cognitive impairment, Cost-effectiveness

## Abstract

**Background:**

A hip or pelvic fracture is a major fall-related injury which often causes a decline in mobility performance and physical activity. Over 40% of patients with hip fracture have cognitive impairment or dementia and poorer rehabilitation outcomes than those without cognitive impairment. In this subgroup, there is a lack of evidence on the best practices supporting recovery. The main aim of this study is to investigate the effects of a transitional care intervention after inpatient rehabilitation on physical activity and functional performance in this group of cognitively impaired patients.

**Methods/design:**

This dual-centre, randomised controlled trial compares a multifactorial intervention with usual care as control condition. Two hundred and forty community-dwellers (≥ 65 years) with a hip or pelvic fracture and mild to moderate cognitive impairment (MMSE 17–26) are recruited at the end of inpatient rehabilitation.

The four-month intervention consists of (a) an individually tailored, progressive home exercise program and physical activity promotion delivered by professional instructors and lay instructors (two home visits per week) and (b) a long-term care counselling approach addressing unmet care needs, pleasurable activities, and caregiver issues if needed. Primary outcome parameters are physical activity, measured as daily walking duration with an accelerometer-based activity monitor (activPAL™) over 72 h, and functional performance, assessed with Short Physical Performance Battery sum scores. Secondary outcome parameters are fear of falling, fall related self-efficacy, falls, quality of life, depression and activity of daily living. Data are collected at the end of rehabilitation, before the intervention at the patient’s home (baseline), after four months (post-intervention), and seven months (follow-up). In addition to completer and intent-to-treat analyses of outcomes, economic data and incremental cost-effectiveness are analysed.

**Discussion:**

Existing service models of volunteer services and legal counselling provided by care counsellors were considered when developing the intervention protocol. Therefore, it should be feasible to translate and deliver the intervention into real-world practice if it has been demonstrated to be effective.

**Trial registration:**

German Clinical Trials Register, DRKS00008863 (Accessed 17 Apr 2019), ISRCTN registry, ISRCTN69957256 (Accessed 17 Apr 2019).

## Background

The high incidence of fall related hip and pelvic fractures as well as the associated negative consequences have been widely described in the literature [1–4]. Mortality rates after hip-surgery are 5 to 10% within 30 days and about 33% after one year [5]. Within six months after fracture, only 40 to 70% regain their prior independence for basic activities of daily living (ADLs) [1]. Between 10 to 20% of hip fracture patients are dependent on long-term care and institutionalised as a consequence of the fracture [1]. Thus, high socioeconomic burden beyond acute care and rehabilitation is apparent [6]. Demographic changes in the future indicate further increases in health and social costs for this patient group [7].

Previous research has identified several predictors for reduced or delayed functional recovery after hip fractures. This includes high age, low pre-fracture level of functioning, reduced walking ability, high prevalence of comorbidities and certain fracture types (e.g. inter−/subtrochanteric versus cervical) [8, 9]. Other factors are fear of falling [10], depression [11, 12] and cognitive impairment [13, 14].

Over 40% of all patients with fall-related hip fracture are cognitively impaired [15]. These patients show poorer mobility outcomes and higher ADL dependence one year after the fracture [13, 16], and in consequence a significantly increased risk of nursing home admission [13].

Although, there is no gold standard intervention for improving mobility after hip fracture [17], structured exercises with appropriate progression and intensity have been found to be effective [18, 19]. While supervised exercise regimes can be implemented easily during inpatient rehabilitation, the continuation of regular, progressive and enjoyable exercise regimes after discharge is challenging. Many people, in particular those with cognitive impairment may prefer to exercise at home rather than attending group sessions. While home based exercise interventions with cognitive behavioural components and minimal supervision can improve physical performance of hip fracture patients without cognitive impairment [20], there is only little evidence derived from subgroup analyses or non-randomised studies for cognitively impaired hip fracture patients. These previous results support that rehabilitation appears to be beneficial for this subgroup, in particular if it is tailored to preferences of the patients in interdisciplinary approaches [21]. However, specific interventions for cognitively impaired patients in the transition from hospital to home which address mobility issues and the need for added support and resources (also for their caregivers) are missing from the literature so far [22].

In contrast to current intervention research for hip fracture patients, comparable research for pelvic fracture patients is lacking. Despite the differences in the (non-) operative treatment of the different fracture types, it is assumed that in early discharge and community rehabilitation both patient groups can be addressed with the same intervention approach.

### Objectives

Primary objective of this study is to compare the effect of a multifactorial home program with usual care on physical activity and functional performance (primary outcomes) in hip and pelvic fracture patients with mild to moderate cognitive impairment. Major components of the post-discharge intervention over four months are supervised exercises, physical activity promotion and long-term care counselling. To increase cost effectiveness and the chances for sustainable implementation, lay instructors deliver a part of the intervention.

Secondary objectives are to evaluate the effect of the intervention on fear of falling, fall related self-efficacy, falls, depressive symptoms, quality of life, and activities of daily living. Economic data and incremental cost-effectiveness will be analysed.

Family caregivers, if existing and consenting to participate, received a specific caregiver counselling and are evaluated in addition to the patients.

## Methods and design

This study is a dual-centre, randomised controlled trial with blinded assessors. Participants (*N* = 240) were randomly assigned to one of two groups (multifactorial intervention or usual care control group) in a 1:1 ratio after initial assessment (−T1) and before discharge from inpatient rehabilitation. Computer-generated random allocation was done by an independent randomisation centre (University of Ulm) and sealed envelopes are used. The randomisation of participants was conducted by the interventionists. The study design is outlined in Fig. 1*.*

**Fig. 1 Fig1:**
[figure not shown]
Study design

### Recruitment

All hip and pelvic fracture patients admitted to the geriatric rehabilitation departments of the Robert-Bosch-Hospital Stuttgart and the Agaplesion Bethanien Hospital Heidelberg (both Germany) were assessed for eligibility from July 2015 to February 2018. To include patients with complications after fracture or surgery, a maximum interval of 3 months between fracture event and admission to rehabilitation was allowed. Patients who had completed any orthopaedic rehabilitation during this time interval were not assessed.

After medical clearing, the screening and the recruiting were planned within the first two weeks of inpatient rehabilitation and done by trained physiotherapists and sports scientists. If it was unclear that the participant could return home the final screening and recruitment procedure was postponed to the third week. Close communication was maintained with the patient, caregiver as well as rehab staff, to avoid unexpected discharge management to nursing home.

Inclusion criteria were a hip or pelvic fracture within the last three months, mild to moderate cognitive impairment (Mini-Mental State Examination score of 17–26 [23]), age ≥ 65 years, minimum visual acuity (corrected vision, Snellen fraction > 20/400), living in home environment or assisted living and ability to walk 4 m with or without walking aid. Exclusion criteria were delirium (identified by the Confusion Assessment Method [24]), severe somatic or mental illness, terminal disease, moderate to severe aphasia (except amnestic aphasia) or severe apraxia, insufficient hearing ability for receiving calls or no telephone accessibility, insufficient knowledge of German language, and place of residence outside the Stuttgart and Heidelberg area, respectively.

Positive screened persons were informed in verbal and written form about the study program and asked to give written consent. The whole procedure was conducted in a comprehensible way according to the recommendations of Appelbaum [25]. Existing legal guardians or authorized representatives were involved in the information and consent process in any case, otherwise the closest family member if possible.

Family members who provided care for the fracture patients and met the following inclusion criteria were also invited to participate in the study: providing care on a non-commercial base for at least 1.5 h per day or 10.5 h per week (assistance of ADLs, instrumental ADLs (IADLs), supervision, including journey time to care recipient’s home), age ≥ 18 years and willingness to engage in a counselling session at the patient’s home. Exclusion criteria were current mental illness or cognitive impairment that affected the ability to give informed consent, to understand the requirements of the assessments or to participate in the intervention, insufficient hearing ability for receiving calls, no telephone accessibility, and insufficient knowledge of German language. Caregiver recruitment (only one caregiver per patient) had to be completed at least during baseline assessment (T1) at the participant’s home.

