### Intervention

#### Overview

The intervention program is outlined according to the TIDierR checklist to ensure a clear and systematic description [26]. The three key components of the multifactorial OF-CARE intervention are physical activity promotion, an individually tailored, progressive, exercise home program (M*odule 1*), and care counselling for the participants and their participating caregivers (if existing) (*Module 2*). Table 1 illustrates the key elements and Fig. 2 the flow of intervention.

**Table 1 Tab1:** OF-Care key elements of the intervention

Key element	Rationale and brief description
*Structure*	
Interventions starting in the patient’s home early after discharge from inpatient rehabilitation	• Exercise continuity after rehabilitation period (transitional care) • Long-term care counselling addressing new support needs and other adaptation issues at home for both, care recipient and caregiver.
Professional exercise instructor (physiotherapist, sports scientist)	• Appropriate exercise selection and progression to improve strength and balance. • Physical activity promotion and goal setting • Addressing fall and safety risks in the patient’s home and during training • Demonstration of additional self-exercises to patient and family member • Training and supervision of lay instructor
Lay-instructor	• Ensuring exercise continuity through regular home visits • Spending some additional time with enjoyable activities together with the fracture patient (positive reinforcement for the whole program)
Social worker	• Assessment of care needs • Organisation of support if necessary (case management) • Addressing caregiver issues
Linking of intervention to long-term care counselling	• Standardized communication and shared analysis of patient’s needs and activity goals between social worker and exercise instructor
*Contents*	
Individual goal setting	• Application of an iconographical card sorting task to facilitate goal setting in this target group • Enhancing intrinsic motivation and training adherence
Exercise program	• Individually tailored, progressive, supervised exercise regime, 2 times per week (details *see* Table 2) • Additional self-exercises to promote activity on the days without supervised training, 1–4 times per week • (Supervised) physical activities, gradual progression by splitting instrumental activities in single components first

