### Outcome measures

Assessments were carried out at 4 measurement time points: -T1 (end of inpatient rehab, only participant), T1 (pre-intervention at participant’s home: week two to six post-discharge), T2 (post-intervention at participant’s home: 4 months after T1) and T3 (follow-up at participant’s home: 3 months after T2). The assessment at -T1 was performed to evaluate the further recovery process between rehabilitation and pre-intervention assessment (T1) and to identify predictors for short-term care and nursing home transition. Because of very short-term decisions on reimbursement of costs for extra rehabilitation time (usually one week or some days of ambulant rehabilitation) added to the 3-week standard rehabilitation regimen it was not possible to deliver the assessment in all cases within a narrow timeframe before discharge. Otherwise these patients have had to be excluded or assessed twice within a week.

Table 3 (participant) and Table 4 (participating caregiver) are outlined according to the SPIRIT Statement [47] and provide an overview of the assessments being performed at the defined measurement time points.

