##### Health and intervention costs

Economic evaluation is conducted by recording total formal and informal care costs, acute and sub-acute hospital days, rehabilitation services and total costs of the intervention. If a patient cannot provide adequate information, his caregiver is asked with the permission of the patient to respond in this domain.

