#### Secondary outcome measures and other measures (participating caregiver)

It is assumed that less than 50% of the patients have family caregivers who meet the inclusion criteria and consent to participate in the study. In contrast to own previous caregiver intervention studies [30, 46], caregivers are included in this study also without showing significant burden, caregiving stress behaviours or depressive symptoms. Therefore, it is expected that the statistical power is not sufficient to detect statistically significant differences in caregiver outcomes between the groups. But with measuring depressive symptoms (CES-D) [73, 74], perceived caregiver competence (SCQ; subscale two: Satisfaction with one’s own performance as a caregiver) [75, 76], quality of life (CarerQoL) [77], physical complaints (GSCL-24; subscale pain in limbs) [78], social problem-solving abilities (SPSI-R:S; subscale: negative problem orientation [79] [80]), leisure time satisfaction (LTS) [81], and frequency of the patients´ behavioural symptoms (RMBPC; subscale frequency) [82], intervention effects can be compared with previous caregiver interventions. Further information on the caregiver outcome measures are published elsewhere [46].

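### Caregivers may be enrolled up to T1, weeks after the patient is randomised, on a criterion tied to a session only one arm receives, so caregiver comparisons are not fully protected by randomisation

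*Protocol article*

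**What the plan says.** - **Patient randomisation.** Methods and design places it after the -T1 assessment and "before discharge from inpatient rehabilitation". The interventionists carry it out, using sealed envelopes. Blinding is stated for assessors only.
- **Caregiver enrolment.** Recruitment sets the outer limit: "Caregiver recruitment (only one caregiver per patient) had to be completed at least during baseline assessment (T1". The words 'at least' can only mean 'at the latest' here. Outcome measures dates T1 to "week two to six post-discharge".
- **Caregiver eligibility.** Recruitment requires "willingness to engage in a counselling session" at the patient's home. It also excludes caregivers whose mental illness or cognitive impairment affects their ability "to understand the requirements of the assessments or to participate in the intervention".
- **Who gets the counselling.** The intervention Overview lists "care counselling for the participants and their participating caregivers (if existing" as a component of the intervention (Module 2) and describes the whole package as added to usual care. The Control group section lists standard care, a calendar and a contact sheet.
- **Use of the caregiver data.** The caregiver outcomes section expects insufficient power but says "intervention effects can be compared with previous caregiver interventions". It does not mention selection after randomisation.

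**The concern.** Randomising patients also balances their caregivers only if the set of caregivers is fixed before allocation can influence who joins. Here it need not be. If a family knows its arm when the caregiver is approached, the willingness criterion asks two different things. In the intervention arm the relative is offered a service. In the control arm the relative is asked to be willing to do something that will not happen, and is then given questionnaires. Fewer control relatives may agree, and those who do may differ in motivation, burden or closeness to the patient.

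What is at stake is the between-arm contrast on caregiver depression, competence, quality of life and the other caregiver measures. Low power, which the article concedes, widens the interval. Selection moves the estimate, and a cautious reading of a wide interval does not correct for that.

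**Working it through.** **1. Order of events**

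| Step | Timing | Section |
|---|---|---|
| Patient randomised | after -T1, before discharge | Methods and design |
| T1 at home | weeks 2 to 6 after discharge | Outcome measures |
| Last moment for caregiver enrolment | T1 | Recruitment |

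A caregiver can therefore be enrolled at least 2 weeks after the patient's randomisation, and up to 6 weeks plus any remaining inpatient days.

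**2. Is the session really confined to one arm?** The Objectives section says that consenting caregivers received counselling and names no arm. The Overview, the add-on statement and the Control group section settle it: the counselling is Module 2 of the intervention. The advice session given to everyone takes place before discharge and is not the home counselling session.

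**3. Number of caregivers.** The article expects fewer than 50% of patients to have a participating caregiver: 240 × 0.5 = 120, so fewer than 120 in total and fewer than 60 per arm if uptake is equal. The standard error of a raw difference is then at least √(2/60) = 0.18 SD.

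**4. Illustrative size, model A.** All uptake and outcome differences here are assumptions; the article gives none. Let a fraction p_int of eligible caregivers enrol in the intervention arm and p_con in control, and let the extra intervention enrollees differ by δ SD from the rest. With no treatment effect,

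shift = (p_int − p_con) / p_int × δ.

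| p_int vs p_con | δ = 0.5 | δ = 0.8 |
|---|---|---|
| 0.9 vs 0.8 | 0.056 | 0.089 |
| 0.9 vs 0.7 | 0.111 | 0.178 |
| 0.9 vs 0.6 | 0.167 | 0.267 |

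**5. Cross-check, model B.** Suppose enrolment follows a latent normal tendency that correlates r with the outcome. The mean among enrollees is r·φ(t)/p, where p is the share enrolled and t is the normal quantile of 1 − p. The factor φ(t)/p is 0.798 at p = 0.5, 0.966 at p = 0.4 and 1.159 at p = 0.3.

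- 50% vs 40%: 0.168 × r, which is 0.03 to 0.08 SD for r = 0.2 to 0.5.
- 50% vs 30%: 0.361 × r, which is 0.07 to 0.18 SD for r = 0.2 to 0.5.

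**6. Effect of the planned adjustment.** Data analyses specifies ANCOVA on T1 scores. If the selected difference is already fully present at T1 and the SDs are equal, the shift shrinks by (1 − ρ). The patient correlations in Sample size, 0.45 and 0.64, are borrowed here as an assumption. The smallest model A value becomes 0.056 × 0.36 = 0.02 SD and the largest 0.267 × 0.55 = 0.15 SD. Differences not captured by the T1 score, such as motivation or the expected course of care, are not removed.

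**The case against.** The strongest reply is that knowledge of allocation is inferred. The article does not say when patients or relatives learn their arm. If they are told only after T1, the willingness criterion filters both arms alike. T1 is also an outer limit: close relatives are involved in the inpatient consent process, so many caregivers may have joined before randomisation, and the share who joined later is unknown. Late closure has a reason too, because the care-hours criterion concerns care being provided, and new needs may show only at home. Finally, the article presents these outcomes as underpowered and mainly for comparison with earlier caregiver studies.

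Most of this stands, and it limits the point to a risk. It does not remove it: blinding is stated for assessors only, the interventionists hold the allocation, and no passage says families are kept unaware. The reason for late closure is also a fair argument for leaving the care-hours threshold as it is.

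A reader might infer three stronger things that the article does not support:

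- **That informal-care cost is inflated in the intervention arm.** Health and intervention costs says "Economic evaluation is conducted by recording total formal and informal care costs". It turns to the caregiver only when the patient cannot give adequate information, and does not limit this to enrolled caregivers. The time burden questionnaire appears in the notes to the caregiver table, but the contents of Tables 3 and 4 are not visible in the text at hand. At most, if informal-care hours come from that questionnaire, this cost component depends on caregiver enrolment and should be read accordingly.
- **That blinded assessors learn the allocation by checking willingness at T1.** The article does not say who recruits caregivers.
- **That the caregiver groups did differ.** No uptake figures are given.

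**Conclusion.** The concern holds as a risk of selection bias in the secondary caregiver outcomes. Three stated facts support it: randomisation before discharge, caregiver enrolment allowed until T1, and an eligibility criterion tied to a session that one arm receives. It also rests on one assumption, that some families know their allocation before the caregiver enrols, which the article neither states nor excludes.

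The size is unknown. The illustrations give raw shifts of about 0.06 to 0.27 SD (model A) or 0.03 to 0.18 SD (model B), and model A falls to roughly 0.02 to 0.15 SD after T1 adjustment under the assumptions shown. The upper raw values are comparable to the standard error of a contrast with at most 60 caregivers per arm, so they could change how a caregiver result is read. Patients consent before randomisation, so late caregiver enrolment does not affect their primary outcomes.

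**What to change.** In Recruitment, require that the caregiver be identified, judged eligible and consented before the patient's allocation is opened.

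Screening ran to February 2018, so for this trial the change has to be made in the analysis and reporting:

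1. Record for each caregiver whether consent came before or after the patient's allocation.
2. Base the between-arm caregiver comparison on those enrolled before allocation, or label the comparison non-randomised.
3. Report caregiver uptake and T1 characteristics by arm.
4. If informal-care hours are taken from the participating-caregiver time burden questionnaire, say so and note that this cost component depends on enrolment.

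The cost is fewer caregivers in a comparison already expected to be underpowered, including the loss of relatives whose caring role becomes clear only after discharge. Item 1 also depends on consent dates being available.
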